## Methods/design

This study is conducted in China as an open-label, multicenter RCT with a parallel group design. Flow chart of the trial is shown in Fig. 1. The procedure and checklist of this trial are shown in SPIRIT figure (Fig. 2) and Additional file 1: SPIRIT checklist, respectively.

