### Randomization

Randomized sequences will be generated by the statistician from Department of Biostatistics, Nanjing Medical university. SAS 9.4 software will be used to generate a random sequence table for the participants. Ninety-six random numbers and the allocation sequence table of the randomized group will be kept as blind codes. The participants will be randomly divided into the oral group (n = 48) and tubing group (n = 48) at a ratio of 1:1. This sequence of randomization will be contained in opaque sealed envelopes and kept by the clinical research coordinator, who will be contacted competitively by each physician to provide the allocation. The principal physicians from the above three centers are responsible for enrolling patients.

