### Oral group

Patients will be instructed to drink 2000 mL polyethylene glycol (PEG) solution over 60 min on the night before the MRE to remove stool and other impurities which may mimic lesions in the MRE. In addition, they will drink 1500 mL 3% mannitol solution gradually in the course of 60 min before MRE. An example of bowel preparation for MRE through oral administering is shown in Fig. 3a. If a patient fails to complete bowel preparation because of severe adverse symptoms such as nausea, vomiting, bloating, and abdominal pain and/or refusing to choose “oral” method, a tube will be placed in his or her mid-gut for MRE. Patients in the oral group will have a soft tube placed in the mid-gut after MRE for enteral nutrition or FMT.

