### Tubing group

Patients will be inserted with a soft tube named mid-gut TET tube (8F, FMT-DT-N-27/1350, FMT Medical, Nanjing, China) in the mid-gut through endoscopy under anesthesia before the bowel preparation for MRE. If patients cannot tolerate endoscopy or anesthesia, a nasojejunal tube will be inserted under digital fluoroscopy. Patients will be instructed to take in 2000 mL PEG solution through the tube over 60 min on the night before MRE. In addition, 1500 mL 3% mannitol solution will be administered through the tube gradually in the course of 60 min before MRE to induce bowel distention. An example of bowel preparation for MRE through mid-gut tubing is shown in Fig. 3b. If a patient refuses the assigned mid-gut tubing before the MRE, or the tube falls off or blocks before the bowel preparation, the patient will be given the option of an alternative method.

All patients will have a colonoscopy examination within 24 h after the MRE. No change in the medical treatment will be made in this study until the colonoscopy examination is finished.

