### Procedures

Over the one-week study period, the included patients will be instructed to answer a questionnaire about their mental pressure and discomfort (such as nausea, vomiting, bloating, abdominal pain, and diarrhea) before/during/after the bowel preparation for MRE. An overview of corresponding assessments is showed in Table 1. Two experienced radiologists will evaluate the grade of bowel distention. Two experienced endoscopists will evaluate the colonoscopy results.

**Table 1 Tab1:** Summary of measures to be collected

Variable				
Visit number/bowel preparation	0/Screening	1/Before	2/During	3/After
Day	~ − 3	− 1	0	1~3
Female-sex (%)	A	–	–	–
Age (years) (mean ± SD)	A	–	–	–
Height (mean ± SD)	A	–	–	–
Weight (mean ± SD)	A	–	–	–
Disease duration (years) (mean ± SD)	A	–	–	–
Disease location (n)	A	–	–	–
Small bowel disease	A	–	–	–
Small bowel + colonic disease	A	–	–	–
Upper GI	A	–	–	–
Perianal disease	A	–	–	–
Previous CD-related surgery (n)	A	–	–	–
HBI	A	–	–	–
Current medication (n)	A	–	–	–
Systematic corticosteroids	A	–	–	–
Thiopurines	A	–	–	–
Mesalazine	A	–	–	–
Anti-TNF	A	–	–	–
Mental pressure (median)	–	A	–	–
Degree of discomfort (median)	–			
Nausea	–	A	A	–
Vomiting	–	A	A	–
Bloating	–	A	A	
Abdominal pain	–	A	A	A
Diarrhea	–	–	–	A
Distention grade (median)				
Jejunum	–	–	A	–
Ileum, proximal	–	–	A	–
Ileum, distal	–	–	A	–
Colon (right part)	–	–	A	–
Colon (left part)	–	–	A	–
Preference to the method (n)	–	–	–	A
MRE lesion detection	–			
Terminal ileum	–	–	–	A
Ileocecal junction	–	–	–	A
Hepatic flexure of colon	–	–	–	A
Splenic flexure of colon	–	–	–	A
Rectosigmoid colon	–	–	–	A

*A* assessed, − not assessed, *SD* standard deviation, *GI* gastrointestinal, *CD* Crohn’s disease, *HBI* Harvey Bradshaw Index, *TNF* tumor necrosis factor

Mental pressure and degree of discomfort: using a visual 5-grade to describe (1 = few, 5 = very severe); distention grade of bowel segments: using a 5-grade scale (1 = 0–20% segmental distention, 2 = 20–40% distention, 3 = 40–60% distention, 4 = 60–80% distention, 5 = 80–100% distention); ileum, distal (the last 20–25 cm of terminal ileum). MRE lesion detection is evaluated by a 5-point scale (lesions locating at the terminal ileum, ileocecal junction, hepatic flexure of colon, splenic flexure of colon, and rectosigmoid colon, consistency of lesion detection from each bowel segment scoring 1 point, otherwise not scoring, confirmed by colonoscopy)

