### Statistical analysis plan

Considering the evaluation for grade of bowel distention, we will calculate the mean, standard deviation, and range of distention scores for each bowel segments and total segments between the two groups by using the Wilcoxon rank sum test. Similarly, we will use the same methods to analyze adverse symptom severity and the accuracy of lesion detection between the two groups. We will compare the proportion of bowel preparation for MRE reaching physician–patient satisfaction score between two groups by using the Chi-square test as our primary analysis. We will also explore the correlations between grade of bowel distention and severity of adverse symptoms by using Spearman’s correlation coefficient. The patients’ preference between the two methods for MRE will be compared using the signed-rank test. All statistical analysis will be done using SPSS software (version 19.0; SPSS Inc., Chicago, IL). *P* < 0.05 will be considered statistically significant.

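### Preference between the two methods is tested as a within-patient comparison, although the parallel design plans no patient to be prepared by both routes

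*Protocol article*

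**What the plan says.** The Methods/design section describes an "open-label, multicenter RCT with a parallel group design", and the Randomization section allocates 48 patients to each arm "at a ratio of 1:1". The Oral group section has patients drink both the cleansing and the distending solution. The Tubing group section gives both through the tube. No crossover is planned.

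Two provisions let a patient meet more than one route. If oral preparation fails or is refused, "a tube will be placed in his or her mid-gut for MRE". If the tube is refused, falls off or blocks before preparation, "the patient will be given the option of an alternative method". Separately, "Patients in the oral group will have a soft tube placed in the mid-gut after MRE for enteral nutrition or FMT", so oral patients receive a tube later, but not for bowel preparation.

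Table 1 (Procedures) lists "Preference to the method (n", a count assessed only at the visit after preparation (day 1 to 3). The Statistical analysis plan section says patients' "preference between the two methods for MRE will be compared" by means of a signed-rank test, under a general threshold of P < 0.05. The primary and secondary outcome sections do not list preference, and it is not part of the satisfaction score that drives the sample size.

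**The concern.** A signed-rank test needs paired or one-sample within-patient data. Applied to a choice between two methods, it takes each answer as one patient's comparison of the two. By design, almost no patient in this trial will have been prepared both ways, so most answers weigh an experience against something not experienced as bowel preparation.

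The imbalance is not the same in both arms. A tubing patient has had the tube placed and both solutions given through it. An oral patient has drunk both solutions and, by the time of the question, may also have had a tube placed, but has not been prepared through it. A tendency to name the familiar method could therefore differ in strength between arms.

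At stake is a P value for preference that no planned within-patient experience supports. It could be read as evidence for the Discussion's expectation that tubing is more acceptable.

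**Working it through.** **Passages side by side.** Patients planned to be prepared by both routes: 0 of 96. Analysis planned for preference: a within-patient test between the two routes. The two do not fit. The protocol gives no figure for the preference outcome, so there is none to reproduce. What follows shows when the mismatch matters.

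**Inputs from the protocol.** 48 patients per arm (Randomization; Sample size calculation); two-sided 5% level (Statistical analysis plan).

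**Assumptions, not in the protocol.**
- The two methods are truly equally liked.
- A share *a* of tubing patients and a share *b* of oral patients name the method they have just had.
- All 96 patients answer, and none switches.
- The choice is coded +1/−1. The coding is not stated. With it, a signed-rank test amounts to a one-sample test of a 50:50 split over all 96 answers.

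**Step 1: the pooled share.** A tubing patient chooses tubing with probability *a*, an oral patient with probability 1 − *b*. With equal arms, the expected pooled share choosing tubing is (*a* + 1 − *b*)/2.

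**Step 2: equal familiarity (*a* = *b* = *s*).** The share is (*s* + 1 − *s*)/2 = 0.50, so the effect cancels. The total choosing tubing is the sum of Binomial(48, *s*) and Binomial(48, 1 − *s*). The test rejects when |total − 48|/√24 ≥ 1.96, that is, at 58 or more or at 38 or fewer. Exact rejection rates:

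| *s* | rejects |
|---|---|
| 0.50 | 5.2% |
| 0.60 | 4.7% |
| 0.65 | 4.2% |
| 0.70 | 3.4% |
| 0.80 | 1.5% |

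No false preference is created; the test becomes slightly conservative.

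**Step 3: unequal familiarity.** Take *a* = 0.70 and *b* = 0.50. The share is (0.70 + 0.50)/2 = 0.60, so the expected total is 57.6 against a rejection limit of 58. The variance is 48 × 0.70 × 0.30 + 48 × 0.50 × 0.50 = 10.08 + 12.00 = 22.08, giving SD 4.70. With continuity correction, P(total ≥ 58) ≈ 1 − Φ((57.5 − 57.6)/4.70) ≈ 51%; exact enumeration also gives 51%. With a smaller gap, *a* = 0.60 and *b* = 0.50, the share is 0.55 and the same enumeration gives 17%. Reversing the gap (*a* = 0.50, *b* = 0.70) gives 51% again, this time mostly in favour of the oral route.

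**Step 4: would a by-arm chi-square test repair it?** Under equal familiarity, the proportion choosing tubing is *s* in one arm and 1 − *s* in the other. The exact Pearson chi-square test with 48 v 48 rejects in 5.2% of trials at *s* = 0.50, 16.9% at 0.55, 51.1% at 0.60, 85.3% at 0.65 and 98.3% at 0.70, all with no true difference in liking. This swap turns a bias that would have cancelled into an apparent effect.

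**The case against.** The strongest reply is that the planned test is not badly hurt. On the pooled reading, symmetric familiarity cancels under 1:1 allocation, as Step 2 shows. That stands. A reader might take the 51%, 85% and 98% in Step 4 as error rates of this trial; they are not, because the protocol plans no by-arm chi-square test of preference. They only warn against one obvious replacement. Harm to the planned analysis needs unequal familiarity. The arms' different exposure makes that plausible, but nothing in the protocol measures its size or direction.

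A reader might also infer that every answer is a guess and that the item can show nothing. The document does not support that. Some patients may experience both routes through switching, although those who switch after failing or refusing a route are a selected group. Oral patients receive a tube after MRE, although whether this precedes the question is not stated. A choice stated after one experience is limited evidence, but not empty.

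Nor is preference the only patient view of the methods. Mental pressure and discomfort are patient-rated for the method received, and the plan compares symptom severity between arms by rank sum. The Discussion does not tie its expectation of acceptability to the preference item, and it defines the patient side of satisfaction by reduction of pain.

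Finally, the questionnaire wording is not shown, so the exact question is unknown. The analysis sentence nevertheless specifies a contrast between the two methods, and a fuller document could not supply experience that the design does not give.

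**Conclusion.** The point holds as a minor one. The plan attaches a within-patient significance test to a preference that, by design, most patients cannot base on having been prepared both ways. An equal pull towards the familiar method cancels in the pooled test. An unequal pull does not: an assumed 20-point gap (70% v 50%) gives about 51% rejections with equal true liking, and a 10-point gap (60% v 50%) about 17%. These rates are illustrations. They rest on assumed shares, a binary coding that the protocol does not state, complete answers and no switching.

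The item is neither primary nor secondary. The primary analysis, the sample size and the between-arm discomfort comparison are unaffected, and the point should not be read as a threat to the trial's main conclusion.

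**What to change.** In the Statistical analysis plan section, remove the signed-rank test of preference. Report stated choice by arm, labelled hypothetical and descriptive, and do not use it as evidence that one method is preferred. Do not substitute a chi-square test of choice by arm.

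For patients still to be enrolled, add two items to the questionnaire and Table 1 that a user of one method can answer: acceptability of the method received, on the existing 5-grade visual scale, and willingness to have it again (yes/no). Compare them between arms with the Wilcoxon rank sum test and the chi-square test respectively.

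The relabelling costs one sentence and applies to all 96 patients. The new items cost two questions. Their downside is that the 29 patients already enrolled at submission of the revised protocol may lack them, leaving at most 96 − 29 = 67 patients with these data. If that is judged not worthwhile, the relabelling alone removes the unsupported inference.

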## Discussion

It has been claimed that inflammation of CD involves the entire gastrointestinal tract. Ileocolonoscopy is useful for detecting inflammation in colon and the terminal ileum. However, this technique cannot detect the inflammation in whole bowel. Recently, new endoscopic techniques have been developed, such as capsule endoscopy (CE) and balloon-assisted enteroscopy (BAE). These techniques have been used for the diagnosis and assessment of disease extent and severity in CD. Because the inflammation of CD is typically transmural, cross-section imaging techniques such as computed tomographic enterography (CTE) and MRE might be superior to endoscopy in visualization of extramural abnormalities such as fistulas and abscesses. The major disadvantage of CTE, however, compared with MRE, is its reliance on ionizing radiation. The mean CT dose index volume for multidetector CTE has been reported to be 4.9 mGy (range, 1.29–12.95 mGy) [24]. Although this dose has decreased in recent years with advances such as iterative reconstruction, it is still higher than that of ionizing radiation-free MRE. In addition, MRE has superior evaluation of perianal disease [25, 26], which is one of the most common and characteristic complications of CD.

Adequate bowel distention during MRE is crucial for the correct evaluation of bowel wall pathologies [27]. Studies have reported that there are two methods of bowel distention—contrast solution administration through nasojejunal tubing and ingestion of oral contrast solution—and a few studies made comparisons between the two methods. Negaard et al. [9] compared the two methods for MRE and demonstrated that bowel distention was superior in nasojejunal tubing. The diameter of the small bowel was larger in MRE after nasojejunal tubing than MRE through administering oral contrast compounds (difference jejunum: 0.55 cm, *P* < 0.001; ileum: 0.35 cm, *P* < 0.001, terminal ileum: 0.09 cm, *P* = 0.08). Masselli et al. [10] compared 22 patients underwent MRE through duodenal tubing with 18 patients through oral administration and demonstrated better bowel distention through duodenal tubing. MRE after duodenal tubing compared with MRE through administering oral contrast was statistically better when visualizing superficial abnormalities (*P* < 0.01). However, Schreyer et al. [28] did not find any significant difference in bowel distention in 21 patients with CD undergoing both two methods of MRE. The procedure of conventional mid-gut tubing for MRE is often the most traumatic part of the examination from the patients’ point of view, which is also considered time-consuming. In addition, one of the methods of tubing has not eliminated radiation exposure. Besides, the whole duration of the examination procedure cannot be separated with a MR compatible pump. The pump was used to enable patients ingest contrast compounds at an infusion rate of 80–150 mL/min. This infusion rate may be so fast that it leads to sever adverse symptoms such as nausea, vomiting, bloating, and abdominal pain [20].

In our study, we will use a novel and quick technique of enteral tubing under gastroscopy named mid-gut TET [11]. In our previous study, 86 patients underwent mid-gut TET and the success rate of the procedure was 98.8% (85/86) [11]. In addition, 97.7% (84/86) of patients were satisfied with the procedure of placement [11]. This mid-gut tube can serve as the delivery way of FMT, enteral nutrition support, and laxative agents and contrast solution for MRE bowel preparation. The laxative agents and contrast solution infusion rate is about 30 mL/min on average. A pump is not needed in the procedure of bowel preparation for MRE through mid-gut tube. Patients can prepare everything by themselves following the physicians’ instructions. They simply need to hang the bottle or sack for laxative agents and contrast solution on the infusion support and fully open the click for controlling the infusion rate. As observed from the pilot study, patients having difficulty in drinking large volumes of solution benefited from mid-gut tubing, with adverse symptoms alleviated or removed. This result is contrary to Negaad’s study probably because of the infusion rate of contrast solution. The infusion rate in Negaad’s study was 120–150 mL/min [20], which is almost 4–5 times of that in our study.

Above all, we assume that the novel, more acceptable, and more time-saving mid-gut tubing for MRE can lead to better bowel distention and less adverse symptoms, and subsequently higher accuracy of lesion detection to reach physician–patient satisfaction. This study aims to provide evidence to support the assumption. Physician–patient satisfaction emphasizes the fact that physicians and patients are satisfied with the accuracy of lesion detection and the reduction of pain, respectively. The results of this study are expected to provide an important basis for the clinical protocol of bowel preparation for MRE in patients with CD.

### Trial status

In total, we have currently included 29 patients in this trial at the time of submission of the revised protocol to *Trials* (20 November 2018). The first patient was included at the Second Affiliated Hospital of Nanjing Medical University.

## Abbreviations

BAE: Balloon-assisted enteroscopy
CD: Crohn’s disease
CE: Capsule endoscopy
CTE: Computed tomographic enterography
DCE-MRI: Dynamic contrast-enhanced magnetic resonance imaging
DW-MRI: Diffusion-weighted magnetic resonance imaging
FMT: Fecal microbiota transplantation
MRE: Magnetic resonance enterography
PEG: Polyethylene glycol
RCT: Randomized controlled trial
TET: Transendoscopic enteral tubing
